|                                 | Duration of the trial:                                                                                                                                                                                                                                                                                                                                                                                                                                                                                                                                                                                                                                                                                                                                                                                                                                                                                                                                                                                                                                                                                                                                                                                                                                                                                                                                                                                                                                                                                                                                                                                                                                                                                                                                                                                                                                                                                                                                                                                                                                                                                                        | 12 months         |
|                                 | Last-patient-out:                                                                                                                                                                                                                                                                                                                                                                                                                                                                                                                                                                                                                                                                                                                                                                                                                                                                                                                                                                                                                                                                                                                                                                                                                                                                                                                                                                                                                                                                                                                                                                                                                                                                                                                                                                                                                                                                                                                                                                                                                                                                                                             | 02/2025 (planned) |
| NUMBER OF PATIENTS       | It is planned to enroll 152 patients                                                                                                                                                                                                                                                                                                                                                                                                                                                                                                                                                                                                                                                                                                                                                                                                                                                                                                                                                                                                                                                                                                                                                                                                                                                                                                                                                                                                                                                                                                                                                                                                                                                                                                                                                                                                                                                                                                                                                                                                                                                                                          |                   |

|                             |                                                                                                                                                                                                                                                                                                                                                                                                                                                                                                                                                                                                                                                                                                                                                                                                                                                                                                                                                                                                                                                                                                                                                                                                                                              |
|-----------------------------|----------------------------------------------------------------------------------------------------------------------------------------------------------------------------------------------------------------------------------------------------------------------------------------------------------------------------------------------------------------------------------------------------------------------------------------------------------------------------------------------------------------------------------------------------------------------------------------------------------------------------------------------------------------------------------------------------------------------------------------------------------------------------------------------------------------------------------------------------------------------------------------------------------------------------------------------------------------------------------------------------------------------------------------------------------------------------------------------------------------------------------------------------------------------------------------------------------------------------------------------|
| NUMBER OF SITES      | n=13                                                                                                                                                                                                                                                                                                                                                                                                                                                                                                                                                                                                                                                                                                                                                                                                                                                                                                                                                                                                                                                                                                                                                                                                                                         |
| PRIMARY ENDPOINT     | 
Primary efficacy endpoint:
Time to first severe exacerbations, defined by hospitalization and/or at least 3 days of systemic steroids or one day of rectal prednisolone (Rectodelt®).
                                                                                                                                                                                                                                                                                                                                                                                                                                                                                                                                                                                                                                                                                                                                                                                                                                                                                                                                                                                                                                      |
| SECONDARY ENDPOINTS  | 
Key secondary endpoint(s): number of severe exacerbations, number of hospitalizations (severe exacerbation), (severe) exacerbation-free survival time, number of asthma-related events defined by use of antibiotics, percentage of night-time awakenings due to asthma symptoms as assessed by the electronic patients diary/PACD, percentage of days without asthma symptoms assessed by TIPP diary App (PACD), , percentage of days and episodes of > 3 days with use of PRN salbutamol rescue medication, health utilization (number of physician visits), number of missed days in daycare, result of TRACK, CGI-C at end of treatment and potential biomarkers for treatment response:
 
Eosinophils, IgE, specific IgE to common allergens (birch, grass, Dermatophagoides pteronyssinus, Alternaria, Cladosporium, cat, dog, hen's egg, cow's milk and peanut.
 
Assessment of safety:
Safety will be ensured by analysis of symptom scores and rescue medication use by the electronic diary, and adverse events (AEs).
                                                                                                                                                  |
| STATISTICAL ANALYSIS | 
Efficacy:
The comparison between groups will be made by time to first severe exacerbation within 12 months of therapy.
 
Description of the primary efficacy analysis and population:
The time to first severe exacerbation will be analyzed by Cox regression with factor treatment and the covariates age group and center. Analyses will be performed in the intention-to-treat population and repeated in the per-protocol population as sensitivity analyses. Treatment differences will be displayed by hazard ratios and 95% confidence intervals.
 
Safety: For safety analyses, frequencies of patients experiencing at least one adverse event (AE) will be displayed by system organ class and preferred term according to MedDRA terminology.
 
Secondary endpoints:
For secondary analyses, Cox regression for time to event data will be used and negative binomial regression for count of events. Further secondary endpoints will be assessed by chi-square or Fisher's exact test for categorical variables or t-test or Mann-Whitney-U-test for continuous variables.
 
All tests will be conducted on a two-sided significance level of alpha = 0.05.
 |

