| TRIAL POPULATION         | 
Main inclusion criteria:
 
 
1. Male or female patients with preschool asthma aged between 1 and 5 years (< 6 at visit 1).
 
2. Physician diagnosed asthma of at least 6 months' history of asthma symptoms, including (but not limited to) wheezing, cough, and/or shortness of breath.
 
3. All patients must have been on maintenance treatment with an ICS at a stable dose, either as mono treatment or in combination with another controller medication, for at least 4 weeks before visit 1.
 
4. Patient was hospitalized due to acute severe asthma and/or was treated with at least 2 courses of systemic steroids (three days of oral steroids or one day of rectal prednisolone 100mg (Rectodelt®)) in the last 24 months before visit 1.
 
5. All patients must be symptomatic (partly controlled or uncontrolled) as defined by the GINA guideline for children aged 5 years and younger in the four weeks prior to screening (visit 1) and randomization (visit 2) despite treatment with ICS (visit 1 and visit 2).
 
6. Patients must be able to inhale from the Respimat® inhaler (with a spacer).
 
 
Main exclusion criteria:
 
 
1. Patients with a significant disease other than asthma such as, but not limited to, the following diagnoses: cystic fibrosis, bronchopulmonary dysplasia, primary immunodeficiency, congenital heart disease, parasitic disease, and foreign body aspiration.
 
2. Patients with clinically relevant abnormal screening hematology or blood chemistry will be excluded if the abnormality defines a significant disease as defined in exclusion criterion.
 
3. Patients with known hypersensitivity to anticholinergic drugs, or any other components of the Tiotropium inhalation solution.
 
4. Patients with any severe acute asthma exacerbation or severe respiratory tract infection defined by systemic steroid intake or hospitalization in the four weeks prior to visit 1.
 
 |                   |

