### 3.6.2 Inclusion criteria

Patients meeting all of the following criteria will be considered for admission to the trial:

1. All patients' parents (or legal guardians) must sign and date an informed consent, consistent with ICH-GCP guidelines and local legislation prior to participation in the trial. In addition, age-appropriate assent in accordance with local regulations or guidelines or both before enrollment in the study and prior to the beginning of any study-specific procedures will be obtained from the child.
2. Ability of parents/legal guardians to understand nature, importance, and individual consequences of the clinical trial.
3. Male or female patients with preschool asthma aged between 1–5 years (< 6 at visit 1).
4. Physician diagnosed asthma of at least 6 months' history of asthma symptoms, including (but not limited to) wheezing, cough, and/or shortness of breath.
5. All patients must have been on maintenance treatment with an ICS at a stable dose, either as mono treatment or in combination with another controller medication, for at least 4 weeks before visit 1.
6. Patient was hospitalized due to acute severe asthma and/or was treated with at least 2 courses of systemic steroids (three days of oral steroids or one day of rectal prednisolone 100mg (Rectodelt®) in the last 24 months before visit 1.
7. All patients must be symptomatic (partly or uncontrolled) as defined by the GINA guideline for children aged 5 years and younger in the four weeks prior to screening (visit 1) and randomization (visit 2) despite treatment with ICS.
8. Patients must be able to inhale from the Respimat® inhaler (with a spacer).

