### **Investigation at (Randomization) visit 2**

All patients must be symptomatic (partly controlled or uncontrolled) as defined by the GINA guideline for children aged 5 years and younger (7) at visit 1 (screening) and before randomization at visit 2.

If this criterion is not met at visit 2, the visit can be repeated once within 2 weeks.

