### **Investigations at visit 2**

- V2 will be scheduled 4-6 weeks after V1
- Inclusion/Exclusion criteria
- Physical examination
- Vital signs
- Height and weight
- Previous and concomitant diseases
- Previous and concomitant treatments
- Spirometry/Oscillometry pre and 30 minutes post-dosing in patients  $\geq 4$  years
- Randomization
- Training of Respimat® inhaler with a Respimat® training device with spacer (Appendix 15.4)
- Dispense of study medication
- Dispense/Check of rescue medication
- Download/review TIPP diary App
- Assessment of asthma control according to GINA guidelines
- AEs
- Concomitant therapy

- Drug accountability

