**Rescheduling prior to randomization (during screening/run-in period)**

- The screening period (between visit 1 and visit 2) may be extended by 7 days (see flow chart), e.g. for administrative reasons.
- In case of severe asthma exacerbation or severe respiratory tract infection (or any other acute illnesses) defined by systemic steroid intake or hospitalization in the 4–6 weeks prior to visit 2, the randomization visit (visit 2) must be postponed until 4 weeks following recovery from the infection or exacerbation.

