### **Investigations at visit 7 (End of trial)**

After a 52-week treatment phase, the last visit 7 will be performed. The end of trial visit may be conducted any time during regular business hours and marks the trial completion that must be recorded in the eCRF.

- V7 will be scheduled  $12 \pm 2$  weeks after V6
- Physical examination
- Vital signs
- Height and weight
- Previous and concomitant diseases
- Previous and concomitant treatments
- Spirometry/Oscillometry  $\geq 4$  years pre-dosing
- Laboratory
- Download/review TIPP diary App
- Check study medication compliance
- Collect study medication/drug accountability
- Assessment of asthma control according to GINA guidelines
- TRACK test
- Complete CGI-C at end of treatment
- AEs
- Concomitant therapy

Please refer to the flow chart (trial schedule and section 3, Figure 2) for the examinations and procedures to be performed in case of early termination of patients who have received at least one dose of study medication.

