## 7 SAFETY

Safety of the study will be ensured by monitoring of symptom score and rescue medication and lung function. Salbutamol pressurized metered dose inhalers (pMDI) via a spacer as needed will be permitted as rescue medication after visit 1 during observation and after randomization throughout the study.

An asthma exacerbation is defined as an increase of rescue medication (RABA) of more than 6 puffs per day compared to baseline and the use of systemic glucocorticosteroids.

Parents are advised to give in case of a severe asthma exacerbation systemic glucocorticosteroids (Celestamine for 3 days according to manufacture; see table 4 Appendix 15.2) by oral route and contact the investigator within 24 hours.

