### 15.2 Dosing table systemic corticosteroids

**Table 4:** Dosing recommendations for systemic corticosteroids (Celestamine®)

| Age of patients | Betametasone (mg)        | Betametasone (ml)      |
|-----------------|--------------------------|------------------------|
| 1-2 years       | Twice daily 1.0-1.0 mg   | Twice daily 2.0-2.0 ml |
| 2-3 years       | Twice daily 1.25-1.25 mg | Twice daily 2.5-2.5 ml |
| 3-4 years       | Twice daily 1.5-1.5 mg   | Twice daily 3.0-3.0 ml |
| 3-5 years       | Twice daily 2.0-2.0 mg   | Twice daily 4.0-4.0 ml |

This dose of Betametasone should be given for 3 days during a severe exacerbation

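### The home steroid table ends with a row labelled 3–5 years, but children can be just under 6 at visit 1 and about 7 at the end of treatment

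*Protocol*

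**What the plan says.** The Protocol's Synopsis admits "Male or female patients with preschool asthma aged between 1 and 5 years", under 6 at visit 1. The inclusion criteria (section 3.6.2) carry the same limit: "Male or female patients with preschool asthma aged between 1–5 years (< 6 at visit 1"). Nothing in the Protocol applies an upper age after that visit.

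Section 5 sets the timing. For randomization, "V2 will be scheduled 4-6 weeks after V1". Two extensions are allowed: "The screening period (between visit 1 and visit 2) may be extended by 7 days", and, where the symptom criterion fails, "If this criterion is not met at visit 2, the visit can be repeated once within 2 weeks". At the other end, "After a 52-week treatment phase, the last visit 7 will be performed", and the trial schedule gives that visit a window of ± 2 weeks.

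Section 7 advises parents to give an oral systemic steroid in a severe exacerbation, with the source stated as "Celestamine for 3 days according to manufacture; see table 4 Appendix 15.2", and to contact the investigator within 24 hours. Table 4 in Appendix 15.2 has four age rows: 1–2, 2–3, 3–4 and 3–5 years. The last ("Twice daily 2.0-2.0 mg") is the oldest. It overlaps the row above it, with a different entry.

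**The concern.** The trial supplies its own dosing table for an instruction that parents may act on before they have spoken to the investigator. That table should reach every age the trial allows a child to have while under treatment, and it stops short.

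The instruction is not a remote contingency. The sample size section assumes that 75% of children on tiotropium and 90% on placebo will have a severe exacerbation within a year, so families can be expected to need it often.

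The gap is also distinct from the overlap at age 3. Relabelling the last row to start at 4 would remove the overlap and leave the upper end as it is, so a correction aimed only at the overlap would miss this.

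**Working it through.** The Protocol states no share of children beyond the table, so there is no figure of its own to reproduce.

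**Inputs from the Protocol:** age 1 to under 6 at visit 1; screening 4–6 weeks, plus up to 7 days, plus up to 2 weeks for a repeated visit 2; treatment 52 weeks, visit 7 ± 2 weeks; 152 randomized; dropout 15%; one-year event rates 90% and 75%. **Assumption:** the age distribution, which the Protocol does not give. The base case is uniform on 1 to under 6, with visit 2 five weeks after visit 1.

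**1. Age at visit 7.** Nominal time from visit 1 to visit 7 is 4 + 52 = 56 to 6 + 52 = 58 weeks, or 1.07–1.11 years. A child just under 6 at visit 1 is therefore about 7.1 at visit 7. With all the windows above, the range is 4 + 50 = 54 to 6 + 1 + 2 + 54 = 63 weeks (1.03–1.21 years). Postponement of visit 2 after an exacerbation could add more.

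**2. Two readings of the last row.** (a) It includes all five-year-olds, so the table ends at the sixth birthday. (b) It ends at the fifth birthday, following the pattern of the rows above. Under (a), children who turn 6 on treatment have no row. Under (b), children enrolled at age 5 have no row from the start.

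**3. Uniform ages.** Let t be the years since visit 1: t0 = 5/52 = 0.096 at visit 2 and t1 = 1.096 at visit 7.

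- Reading (a): share uncovered = t/5. At visit 7, 1.096/5 = 21.9%, and 0.219 × 152 ≈ 33 children. Average over treatment: [(0.096 + 1.096)/2]/5 = 11.9%. Over the 54–63 week range, the visit 7 share is 20.7–24.1%.
- Reading (b): share uncovered = (1 + t)/5. At visit 1, 20% (about 30 children). At visit 7, 2.096/5 = 41.9% (about 64 children). Average over treatment: 31.9%.
- With 15% dropout unrelated to age, reading (a) at the nominal 56–58 weeks gives 0.85 × 21.5–22.2% ≈ 18–19% of all randomized. Among completers the share stays near 22%.

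**4. Other age distributions.** Take a linear density with r = density at age 6 divided by density at age 1, and g = 56 weeks = 1.073 years. The share at visit 7 is L[r + (1 − r)L/10] / [2.5(1 + r)], with L = g for reading (a) and L = 1 + g for reading (b).

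| r | (a) at visit 7 | (b) at visit 7 |
|---|---|---|
| 0 | 4.6% | 17.2% |
| 0.25 | 11.4% | 26.9% |
| 0.5 | 15.8% | 33.4% |
| 1 (uniform) | 21.5% | 41.5% |
| 2 | 27.1% | 49.6% |

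The uniform row differs slightly from step 3 because it uses 56 weeks, not 57.

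**5. Share of first events, reading (a), uniform ages.** With a constant hazard h and one-year event-free proportion S, and ignoring dropout, the mean time of first events within the year is 1/h − S/(1 − S).

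- Placebo: h = −ln 0.10 = 2.303; mean 0.434 − 0.111 = 0.323; share (0.096 + 0.323)/5 = 8.4%.
- Tiotropium: h = −ln 0.25 = 1.386; mean 0.721 − 0.333 = 0.388; share (0.096 + 0.388)/5 = 9.7%.

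**The case against.** The strongest reply is that this is a short appendix matter whose size is easily overstated. Much of that stands.

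- **A fifth as a floor.** A reader might infer that at least a fifth of families end up outside the table. The documents do not support a floor. The figure is the uniform-age result at the last visit, and with younger children it falls to about 5–16%. Visit 7 is also the worst moment: averaged over treatment the share is about 12%, and among first events about 8–10%. For a standing safety instruction, treatment time is the fairer summary, because later exacerbations call on the table too.
- **The strict reading.** The Protocol itself uses 1–5 years to mean up to the sixth birthday, which favours counting five-year-olds in the last row. The row pattern points the other way, but in a table that already has an apparent labelling error. The figures under reading (b) should be held as the less likely case.
- **The primary endpoint.** A reader might infer that whether an episode in an older child counts depends on the missing row. It does not. The endpoint is hospitalization and/or at least 3 days of systemic steroids or one day of rectal prednisolone, with no age, product, dose or table row in it. Nor is there any sign of bias between arms in a randomized, double-blind comparison.
- **Families left with nothing.** A reader might infer that parents must guess or withhold treatment. Section 7 also refers to the manufacturer and requires contact within 24 hours, and the diary instructions leave the child's systemic steroid to be named by the nurse or coordinator. The text shows no row in the trial's own table; it does not show the absence of any dose source.
- **A caregiver sheet.** No section says that Table 4 itself is handed to families.

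None of this closes the gap. Under either reading, some children on treatment are of an age the table does not list.

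**Conclusion.** The point holds as an internal inconsistency in a safety instruction. The entry limit binds only at visit 1, treatment runs for a year after that, and the table to which section 7 refers has no row beyond 3–5 years. That conclusion needs no assumption about ages.

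Its size does. On the more natural reading of the last row and uniform ages, about 22% of children (33 of 152) are past the table at visit 7 and about 12% of treatment time is uncovered. Plausible skews move the visit 7 share from about 5% to about 27%. If the last row ends at the fifth birthday, the uniform figures are 20% at visit 1 and about 42% at visit 7.

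It should be corrected because it concerns home treatment of severe exacerbations, which the plan expects to be common. It is not a threat to the primary analysis.

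**What to change.** The responsible clinicians should reconcile Table 4 with the age criterion and the 52-week treatment period, so that non-overlapping rows cover every age a child can reach between visit 1 and visit 7. The overlapping 3–4 and 3–5 rows should be resolved in the same edit. Section 7 should then agree with the revised table, and any caregiver instruction derived from it should be updated. Which doses belong in which rows is for those clinicians; none is proposed here.

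The cost is a correction to one appendix table, plus redistribution of any caregiver material that depends on it. The design, endpoint definition, sample size and analysis are untouched.
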